### Study aims & quantitative hypotheses

This study’s primary objective is to assess the effectiveness of a health literacy intervention (i.e., the University of California San Diego Re-Entry Community Linkages [UCSD RELINK] Program) for improving JIA’s healthcare access. Our specific aims for this longitudinal, mixed-methods randomized clinical trial (RCT) are to quantitatively assess the impact of the UCSD RELINK coach-guided health literacy intervention (i.e., health coaching and service navigation) vs. a control group (i.e., self-study of the health coaching program, and brief service navigation support) on healthcare utilization at 6-months and maintenance at 12-months. Secondary quantitative outcomes include assessing health insurance coverage and having a usual source of care. Using qualitative methods, we also seek to understand the impact and maintenance of the intervention at 6 and 12-months.

We hypothesize that participants receiving the coach-guided health literacy intervention will be more likely to report healthcare use at 6 months versus those assigned to the self-study control group. Similarly, we hypothesize that coach-guided health literacy intervention participants will be more likely to report having 1) health insurance and 2) a regular source of care at 6 month follow-up versus control group participants. Maintenance of these outcomes will be assessed quantitatively at 12 months. Additional exploratory outcomes include the types of health services used, type and continuity of health insurance coverage, reasons for being uninsured, delayed care seeking (i.e., has delayed getting medical care in the past 6 months), number of days in hospital, and satisfaction with care.

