### Power & sample size

A total of 300 individuals will be enrolled into the study. The power calculation was based on the primary outcome of recent healthcare utilization over the study period (yes/no) and analyzed with a mixed-effects logistic regression. Power was conservatively calculated for recent healthcare utilization at baseline, 6 and 12-months based on the assumption that 60% of the treatment group and 40% of the control group would report recent healthcare use (Ojeda et al., 2021). Accounting for an intraclass correlation coefficient of 0.4 and considering 30% attrition (of the 300 enrolled at baseline), we anticipate we will need 208 participants (104/group) to detect an odds ratio of 1.8 of recent healthcare utilization between the intervention and control group with at least 80% power and 0.05 two-tailed alpha.

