### Statistical analyses for survey data

A separate password-protected document with participants’ names and study ID number managed by the database administrator will enable linkage of all surveys. Statistical analyses will incorporate the intent-to-treat (ITT) principle. Participants who are randomized will be included in the ITT population. A mixed-effects logistic regression (Liu, 2015) will be used to analyze the effect of the coach-guided intervention on the primary outcome, recent healthcare utilization (yes/no) over the study period. This approach captures the between-individual and within-individual variability due to the repeated measures. Time invariant covariates include gender and age at baseline in addition to other predisposing, enabling, and health behavior variables determined to be unbalanced at baseline (univariate *p* < 0.10) and associated with the outcome (univariate *p* < 0.15). Time-varying covariates include follow-up time, treatment assignment (intervention vs. control), and time-by-treatment interaction terms. The maximum likelihood estimation approach used in the mixed-effects model enables us to incorporate all participant data even among those with only baseline measures. Analyses will be conducted using Stata v16 (StataCorp., 2019). Methods analogous to the analysis of the primary outcome will be applied to secondary outcome measures: 1) health insurance and 2) a regular source of care. Bonferroni’s correction will be applied for multiple testing of secondary outcomes, so statistical significance will be compared to a *p* < 0.025.

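### Bonferroni at 0.025 for the two named secondary outcomes is valid, but Holm's step-down procedure keeps the same 5% familywise bound and never rejects less

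*Protocol article*

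**What the plan says.** Under Statistical analyses for survey data, methods analogous to those for the primary outcome "will be applied to secondary outcome measures: 1) health insurance and 2) a regular source of care". The same paragraph ends with the multiplicity rule: Bonferroni's "correction will be applied for multiple testing of secondary outcomes, so statistical significance will be compared to a" p-value below 0.025. No step-down or other sequential rule is mentioned.

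Study aims & quantitative hypotheses names the same pair: "Secondary quantitative outcomes include assessing health insurance coverage and having a usual source of care". It states a directional hypothesis for each of them at 6 months.

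The level for the secondary family is not given in words. Power & sample size plans the primary comparison "with at least 80% power and 0.05 two-tailed alpha", and 2 × 0.025 equals that 0.05.

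**The concern.** The article itself fixes the method and the threshold, so this is not a detail left to an unseen analysis plan. With two tests, a fixed 0.025 for both is more demanding than a 5% familywise bound requires. Once one hypothesis has been rejected at 0.025, only one remains that could be falsely rejected, and it can be tested at the full 0.05.

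At stake is the second of the two secondary hypotheses. Suppose one outcome is clearly significant and the other gives a p-value between 0.025 and 0.05. The plan must then call the second one not significant, although a rule with the same bound would not. The sample size rests on healthcare use alone, so no power was set aside for these two outcomes.

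**Working it through.** **Inputs from the protocol article.** Two outcomes in the corrected family and a threshold of 0.025 (Statistical analyses for survey data). Two-sided 0.05, 104 per group (Power & sample size). The article gives no secondary-outcome rates by arm, so every power figure below is an assumption.

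**The plan's own figure.** 0.05/2 = 0.025, which reproduces. With independent tests the familywise error is 1 − 0.975² = 0.0494; the upper bound under any dependence is 0.05.

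**Holm for two tests.** Compare the smaller p with 0.025. If it is significant, compare the larger with 0.05. Any result significant under Bonferroni is also significant here.
- *Both nulls true.* A false rejection needs the smaller p to pass 0.025, exactly as under Bonferroni. Simulation (2,000,000 draws) gives the same error for both rules: 0.0495, 0.048 and 0.045 at test-statistic correlations of 0, 0.3 and 0.6.
- *One null true.* Its p-value never meets a threshold looser than 0.05, so the bound holds. The actual error does rise. If the other outcome has 80% power at 0.05, error on the true null is 0.025 under Bonferroni and 0.043, 0.042 and 0.040 under Holm at the three correlations.

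**Size of the gain, independent tests.** Let *a* be each outcome's power at 0.05 and *b* its power at 0.025.
- Both significant: Bonferroni *b*²; Holm *a*² − (*a* − *b*)²; gain 2*b*(*a* − *b*).
- Per outcome: Bonferroni *b*; Holm *b* + (*a* − *b*)*b*; gain *b*(*a* − *b*).
- At least one significant: 1 − (1 − *b*)² under both rules.

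| *a* (assumed) | *b* | Both: Bonferroni | Both: Holm | Gain, both | Gain, per outcome |
|---|---|---|---|---|---|
| 0.20 | 0.130 | 0.017 | 0.035 | 0.018 | 0.009 |
| 0.30 | 0.210 | 0.044 | 0.082 | 0.038 | 0.019 |
| 0.60 | 0.489 | 0.239 | 0.348 | 0.109 | 0.054 |
| 0.70 | 0.596 | 0.355 | 0.479 | 0.124 | 0.062 |
| 0.80 | 0.712 | 0.507 | 0.632 | 0.125 | 0.062 |
| 0.95 | 0.914 | 0.835 | 0.901 | 0.067 | 0.033 |

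For *a* = 0.80: 0.712² = 0.507, and 0.80² − (0.80 − 0.712)² = 0.632.

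**Correlated tests, *a* = 0.80.** At correlations 0, 0.3 and 0.6, the chance of showing both goes from 0.51, 0.54 and 0.59 to 0.63, 0.66 and 0.69. Per-outcome power goes from 0.71 to 0.78, 0.77 and 0.76.

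**Illustration with the pilot changes.** Pilot study reports uncontrolled rises in insurance from 64% to 88% and in a usual place of care from 55% to 70%. Take them, as an assumption only, as differences between arms at 104 per arm:
- Insurance: 0.24 / √[(0.88×0.12 + 0.64×0.36)/104] = 4.22.
- Source of care: 0.15 / √[(0.70×0.30 + 0.55×0.45)/104] = 2.26.
- Power for source of care is 0.51 under Bonferroni and 0.62 under Holm. Insurance barely moves, from 0.976 to between 0.977 and 0.982. Both: 0.50–0.51 against 0.61–0.62.
- With half the insurance effect (76% against 64%), both: 0.19–0.28 against 0.28–0.38, over the three correlations.

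**The case against.** The plan pre-specifies a valid, conservative and widely used correction, and its arithmetic is right. A reader might infer from this point that 0.025 is a mistake or that the secondary results would be unsound. Neither follows: the fixed threshold protects the error rate at least as well as Holm does. This is an improvement in efficiency.

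Three other stronger readings also fail.
- *Holm leaves the error rate unchanged.* Only the 5% bound is unchanged. When one effect is real, error on the other, true null rises from 0.025 to about 0.04. The added power comes from alpha that Bonferroni leaves unspent.
- *The gain is 11 to 12 points.* That is close to the maximum. The control arm receives the curriculum, the website, two navigator sessions and a referral report (Control arm: self-study group), so differences between arms may well be smaller than the uncontrolled pilot changes. At low power the gain is a few points.
- *The family is settled as two tests at 6 months.* The paragraph with the correction names two outcomes but no visit, and its model covers the study period with time-by-treatment terms. Dependent variables lists further secondary outcomes, such as insurance type and continuity, delayed care and hospital days. Study aims calls several of these exploratory. The abstract lists insurance and a regular source of care among the primary outcomes. The two-step rule is Holm's rule only for a family of two.

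Bonferroni also gives simpler simultaneous confidence intervals. All of this limits the size of the gain and how the fix is worded. It does not alter the fact that, for a given family, Holm rejects at least as much within the same bound.

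**Conclusion.** The point stands as a minor, optional improvement. Holm controls familywise error at 5% under any dependence and never rejects less than the fixed 0.025 rule. The benefit falls only on the outcome with the larger p-value, and only when one p-value is at or below 0.025 and the other lies between 0.025 and 0.05.

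On the assumption of independent tests with equal power, the gain in showing both outcomes runs from about 2 points at 20% power, through a peak of about 12 points near 70 to 80%, to 7 points at 95%. Positive correlation reduces it slightly: at 80% power it is still about 10 points at correlation 0.6. The article cannot place the trial within this range, because it gives no expected rates by arm for either outcome.

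**What to change.** Before any unblinded analysis:
1. Confirm that the corrected family is the two outcomes named under Statistical analyses for survey data, and align the abstract, Study aims and Dependent variables with that.
2. State that each is tested on the same treatment contrast that the plan uses for the primary outcome.
3. Replace the fixed threshold with Holm's procedure: the smaller p-value against 0.025 and, if that is significant, the other against 0.05. If the family turns out to be larger, use the Holm steps for that size.

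The swap itself is one sentence; the first two steps are short clarifications. Sample size, data collection and conduct are unaffected. The costs are less simple simultaneous confidence intervals and the use of part of the alpha that Bonferroni leaves unspent.

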### Analysis of key secondary outcome (safety)

All participants will be included in a safety analysis. Adverse Events (AEs) and Serious AEs (SAEs) will be listed by participant. AEs will be summarized by method of collection type, frequency, severity, relationship to study intervention, any change in study intervention, and number of participants per treatment. The frequency of AEs and SAEs will be described by group and compared using Fisher’s exact test.

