### Interventionist credentials & training

For this study, the interventionists will include Health Coaches and Service Navigators. *Health Coaches* will have graduate-level training as licensed therapists (e.g., Marriage & Family Therapist), prior experience serving JIA and deep knowledge about the region. *Service Navigators* will be community members with lived experience or history of serving JIA by providing community resources per participants’ needs (e.g., gender, race/ethnicity, faith, geographic region, income level). Navigators may have university-based education (e.g., Associate of Arts, Bachelor of Arts, Master of Public Health, etc.) in fields adjacent to social services or health professions, but this is not required. Service Navigators will have established relationships with local institutions that explicitly serve the study’s target population.

Health Coaches will undergo standardized training of the intervention, including studying written training manuals, the Health Coaching curriculum workbook, and training videos that describe the intervention philosophy, components and staff roles. Health Coaches will also meet with the principal investigator (PI), project manager, data analyst, and lead mental health faculty advisor to complete the training. The Health Coaches will have prior training in the use of patient-centered, team-based, trauma-informed, and strengths-based care, Mental Health First Aid, de-escalation techniques, SMART Goal Setting, and Case Management (Bath, 2008; Berghuis, 2018; Bjerke & Renger, 2017; Brun & Rapp, 2001; Conzemius & O'Neill, 2009; Epstein & Street, 2011; Gelkopf et al., 2016; Hadlaczky et al., 2014; King, 2017; Levenson & Willis, 2019; Rapp, 1998; Richmond et al., 2012; SAMHSA, 2014a, 2014b; Wallace et al., 2011; Woods et al., 2013). Service Navigators will be trained in the study’s resource directory and key partners and best practices in survey administration and how to administer the online baseline intake survey. Service Navigators and Health Coaches will be trained in documenting services provided, incentives, and adverse events using the study’s case management system. The Health Coach and Navigator will receive ongoing supervision and annual refresher training. Administrative staff (i.e., PI, project manager, data analyst) will meet weekly with the staff to debrief.

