**Service Navigation**		
Introduction to Service Navigator	** + **	** + **
Weekly Case Management Meetings (30 min; 12 sessions over 6 months)	** + **	**–**
Review of Service Navigation Plan	** + **	** + **
Intervention Delivery Mode	Real-time sessions; Emailed and written referral list	Emailed and written referral list
**Weekly study participation reminders**	** + **	** + **

If this item is provided, it is represented as: “ + ”

If this item not provided, it is represented as: “—”

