### Treatment arm: coach-guided intervention

Participants randomized to the treatment arm will work with their assigned Health Coach and Service Navigator; sessions are scheduled on days/times that are convenient to staff and participants. Participants will engage with the 12-module health literacy curriculum during weekly sessions with their Health Coach, using the curriculum workbook or program website, per their preference, to facilitate learning and exercise completion. Health Coaches will meet with participants during 12 sessions lasting ~ 45 min throughout a 6-month period. The Health Coach will tailor the curriculum per their needs and interests and guide each participant through the reflection exercises. The curriculum is designed for in-person delivery but can also be implemented by video or phone sessions to ensure continuity of the intervention.

Participants will also receive up to 12 sessions of Service Navigation support, per participant preference, lasting 30-min over a 6-month period. At baseline, the Navigator will conduct the intake survey in order to develop the service navigation plan which identifies resources for participants’ most pressing immediate needs. Navigators and Health Coaches will assist with linkage to resources, goal-setting, and mentoring participants through role-playing and modeling of behaviors that support healthcare access and encourage participants to practice new communication and preventive-care skills in real-world settings (e.g., preparing for healthcare visits, self-advocacy). In partnership with the Health Coach and Service Navigator, participants will reflect on barriers and facilitators and develop personalized solutions to support healthcare service utilization. Participants will also receive a written and electronic emailed Service Navigation report including providers’ contact information for independent follow-up.

Importantly, the intervention adopts a team-based approach: the staff support participants through targeted monitoring meetings to support participant self-management, successes, to anticipate new needs, or exchange resources that may impact their shared work. This approach is influenced by the Collaborative Care Model (CCM); for example, CCM has been successfully used with reentrants for care coordination and service linkages across cross-disciplinary teams (Kim et al., 2019).

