### Control arm: self-study group

Participants assigned to the control arm will work with their assigned Service Navigator for two sessions. During the first session, participants will receive the Health Coaching and Service Navigation workbooks, complete the baseline intake service navigation survey, and will be instructed that they will independently engage with the curriculum using the workbook or the study website (via a personalized log-in which tracks module completion). During the first session, the Service Navigator will assist the participant to establish their study website log-in credentials and how to access the Health Coaching modules on the study website. Participants who prefer to complete the printed curriculum will be instructed to submit photographs of the completed workbook pages to the study email to receive certificates of completion; these may be shared with their supervising officer or the court to demonstrate participation in activities that can benefit the participant reenter the community. During the second study visit, participants will receive a printed and digital (emailed) service navigation report which identifies recommended service providers and resources, including contact information so the participant can access these resources independently. Participants will have opportunities to ask clarifying questions at this visit and no further contact with the Service Navigator will occur.

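### The between-arm adverse event test is open to ascertainment bias: the only named recorders meet the treatment arm up to 24 times and controls twice

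*Protocol article*

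**What the plan says.** **Who records.** Under Interventionist credentials & training: "Service Navigators and Health Coaches will be trained in documenting services provided, incentives, and adverse events", in the study's case management system. No other recorder of adverse events is named.

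**Contact, treatment arm.** Under Treatment arm: "Health Coaches will meet with participants during 12 sessions lasting ~ 45 min throughout a 6-month period". For navigation: "Participants will also receive up to 12 sessions of Service Navigation support, per participant preference, lasting 30-min over a 6-month period". Table 3 shows the same two series of sessions for this arm only.

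**Contact, control arm.** Under Control arm: "Participants assigned to the control arm will work with their assigned Service Navigator for two sessions". The first session includes the baseline intake survey. After the second, "no further contact with the Service Navigator will occur". Table 3 gives controls no Health Coach.

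**Analysis.** Under Analysis of key secondary outcome (safety), all participants are included, events are listed by participant, and they are summarised by, among other things, how they were collected. Then: "The frequency of AEs and SAEs will be described by group and compared using" Fisher's exact test.

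**Other contacts.** Follow-up surveys & incentives describes survey visits at 6 and 12 months and monthly check-ins in months 7 to 12, neither limited to one arm. Their stated purposes are measuring use of health-supporting institutions and retention. Adverse events are not mentioned there.

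**The concern.** Fisher's exact test is a sound test for two proportions. The difficulty lies in what is put into it. In this trial, contact with the staff who record events is part of the intervention, so the chance that an event is noticed and written down differs between arms by design. Randomisation does not remove this, because the difference arises after allocation.

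If true risk is equal, more complete recording in the treatment arm looks like harm from coaching. If the intervention does cause harm, the same excess could be put down to closer observation. Safety is headed as a key secondary outcome, so a p-value from this comparison is likely to be read as evidence in either direction.

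**Working it through.** **1. Contacts with the named recorders, months 0 to 6**

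- Treatment: 12 coaching + up to 12 navigation = up to 24.
- Control: 0 coaching + 2 navigation = 2.
- Ratio: 24 / 2 = 12 at the maximum. Navigation sessions depend on participant preference. With none taken up beyond coaching, the comparison would still be 12 against 2.
- The first control session is the baseline intake, so only the second can bring up an event that occurs afterwards. The article does not date the second session.

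**2. Is there a stated figure to reproduce?** No. The article gives no adverse event rate, capture rate, significance level or power for the safety comparison. What follows is an illustration.

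**3. Set-up**

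- From the article: 300 enrolled, 1:1, so 150 per arm. The sample-size section uses 104 per arm after attrition.
- Assumed: true risk r of at least one event, equal in both arms; capture probabilities c_T (treatment) and c_C (control); two-sided 0.05 test; independent participants.
- Observed proportions: p_T = r × c_T and p_C = r × c_C.
- False rejection = sum over all pairs (x, y) of Bin(x; n, p_T) × Bin(y; n, p_C), counting the pairs where the exact Fisher p-value is at most 0.05.

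**4. Results, 150 per arm, no true difference in harm**

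| True risk | Observed at 90% vs 50% capture | Rejects | Observed at 90% vs 70% capture | Rejects |
|---|---|---|---|---|
| 20% | 18% vs 10% | 45.6% | 18% vs 14% | 12.1% |
| 10% | 9% vs 5% | 20.2% | 9% vs 7% | 6.5% |
| 5% | 4.5% vs 2.5% | 8.2% | 4.5% vs 3.5% | 3.4% |
| 3% | 2.7% vs 1.5% | 3.8% | 2.7% vs 2.1% | 2.1% |

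Nearly all of these rejections point to excess harm in the treatment arm. With 104 per arm and a 20% risk, the two figures are 31.1% and 8.7%.

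**5. The same test with equal capture.** At 90% in both arms and 150 per arm, it rejects 3.5%, 3.2% and 2.3% of the time at true risks of 20%, 10% and 5%. The excess in step 4 therefore comes from unequal capture and not from the test.

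**The case against.** The strongest reply is that the article trains coaches and Navigators to document events but does not call them the only source. The planned summary by method of collection implies more than one method. The surveys and check-ins reach both arms, and how events are elicited is the kind of detail an article leaves to the full protocol. The summaries by collection method and by relationship to the intervention would also help a reader see whether an excess comes from session reports.

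Much of this stands. A reader might infer that every adverse event reaches the database through the interventionists, or that the comparison cannot be interpreted at all. The article supports neither. If the surveys ask the same questions in both arms, the bias shrinks. It does not vanish while session reports, which come mainly from one arm, enter the same test. The summary by method is descriptive and places no limit on the test. The recorders, the contact schedule and the test are all stated in the article, so the point does not rest on its silence alone.

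A reader might also infer that the test will be run on event counts, so that repeated events in one person break its independence assumption. The wording does not establish this. Events are listed by participant and the number of participants is summarised, so a test on participants with at least one event is a natural reading.

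Finally, the illustration depends on the event risk. At 5% with a modest capture gap, or at 3% with either gap, rejection stays below 5%. Few events are plausible for an education and navigation programme, and the article does not settle the matter.

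**Conclusion.** The point holds in a limited form. Followed as written, the plan compares arms on events whose only named recorders see one arm up to 12 times as often as the other, with no restriction to events collected alike. The expected direction is apparent excess harm in the treatment arm.

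The size is unknown. Under the assumed capture rates, with 150 per arm and true risks from 5% to 20%, false rejection runs from about 3% to about 46%. It is material when events are common and the capture gap is wide, and negligible when events are rare. The primary efficacy analysis is unaffected. The change is worth making because it is cheap and the comparison is presented as a key secondary outcome.

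**What to change.** - Ask identical adverse event and serious adverse event questions of both arms at the existing 6- and 12-month surveys. If the instruments already do so, state it.
- Base the between-arm Fisher's exact test on the number of participants with at least one event elicited that way.
- List session-reported events separately by arm, without a test, and keep the planned summary by method of collection.
- Keep all serious adverse events, from any source, in the descriptive listing.
- Report by arm how many participants completed the survey questions.

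The cost is a few survey items and a sentence or two in the safety section. There are two downsides. Fewer events enter the test, so it has less power. Survey-elicited events also miss participants lost to follow-up, expected to be about 30%, and that loss may differ between arms. Reporting completeness by arm and listing all serious events are there to make this visible.
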